***Quality control, data collection and management***

Trained research staff collect trial data carefully according to a standard protocol and complete paper case report forms (CRFs) accurately, completely, timely and reliably.

To keep the information confidential, the experimental data including primary and secondary outcomes will be carefully recorded in CRFs which will be identified by IDs rather than identifiable information and will be stored separately and securely in the linking document. To guarantee the data quality, the completed CRFs will be input in Microsoft Access by two researchers. For some emergent reasons, investigators were bound to

During the study, the First Affiliated Hospital of Wenzhou Medical University is responsible for making regular visits (once a week) to review trial conduct, and the Ethics Committee will monitor for protocol violations weekly, there was no conflict of interest with the sponsors or researchers.

**STATISTICAL ANALYSIS**

We will use log-rank test for the primary outcome, if the influence of confounding factors needs to be considered, Cox proportional hazard model can be used. For all secondary outcomes, Wilcoxon rank sum test will be used. For safety evaluation of TCM, two-sided t-test will be applied to each safety measurement after data normalization.

To better understand the nature the missing mechanisms, we will characterize the type of subjects who have missing data, then statistical models to impute missing values if the assumption of missing at random is met will be used.

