**Sample size**

Based on previous clinical practice of using TCM fought against SARS and H1N1 influenza patients [23], it is estimated the median survival time in the TCM group as 3 days, and 1.5 times longer in the control group. Concerning the analysis of the primary endpoint, the duration of time before improvement of at least one of the common cold-like symptoms (fever, cough, malaise, shortness of breath) , will be estimated using the Kaplan-Meier method, and

the survival curves will be compared between groups using the log-rank test. And this study is designed to detect a statistically significant difference with a level of 5% and a power of 70% (one-sided type-1 error of
[figure not shown]
 =5%，
[figure not shown]
 =30%), so approximately 61 participants in each group will be needed. Thus, under the prediction of a dropout rate of 10%, the sample size of 140 participants will be sufficient to detect a clinically important difference in this trial.

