**MEASUREMENTS**

***Primary Outcome***

The primary outcome will be the number of days until the clinical symptom of fever improves in the first 14 days of treatment following randomisation. Fever will be defined as an improvement when the temperature is less than 37℃.

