***Safety outcomes***

Test safety will be monitored during this trial. Participants will accept a routine physical examination, including breath rate, heart rate, temperature, blood pressure, weight, routine urine test, routine blood test, liver, kidney function tests, and an electrocardiogram.

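### The primary log-rank test leaves baseline temperature unused by plan, and the optional Cox clause names neither a covariate nor a trigger, so power may be lost and adjustment could be chosen after the data are seen

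*Protocol*

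**What the plan says.** All references are to the protocol.

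- **Statistical Analysis:** "We will use log-rank test for the primary outcome". The sentence continues: "if the influence of confounding factors needs to be considered, Cox proportional hazard model can be used". No covariate is named, and nothing says what would show that confounding needs considering.
- **Primary Outcome:** days until fever improves within 14 days, where "Fever will be defined as an improvement when the temperature is less than 37℃".
- **Safety outcomes:** the routine examination covers several measurements, "including breath rate, heart rate, temperature, blood pressure, weight". Fig. 2 marks routine inspection at D0. The TCM Syndrome Scoring System also grades fever (0, 2, 4 or 6) at baseline.
- **Randomization:** 1:1 by minimization, with pneumonia severity as the only balancing factor.
- **Inclusion criteria:** mild symptoms are enough for entry; fever is not required.
- **Sample size:** the same log-rank comparison, planned for a "difference with a level of 5% and a power of 70"% and described as "one-sided type-1 error of" 5%. The effect is given as "it is estimated the median survival time in the TCM group as 3 days, and 1.5 times longer in the control group", leading to "approximately 61 participants in each group will be needed".

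**The concern.** When the event is crossing a fixed temperature line, a patient's distance above that line at entry plausibly affects how soon the line is crossed. A patient entering at 37.2℃ may meet the definition at the next reading; one entering at 39.5℃ must cool by more than 2.5 degrees. If the primary test ignores this, the variation stays in the comparison and dilutes the treatment effect seen at the level of the whole arm. A trial planned at 70% power has little room for that.

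The second issue is the Cox clause. It permits adjustment but does not commit to it. Because it names no covariate and no trigger, whoever runs the analysis could decide on adjustment, and on the variables, with the data in hand. Two primary results would then be available. An optional adjustment also cannot be counted towards planned power.

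**Working it through.** **1. Reproduce the plan's sample size.** Inputs from Sample size: medians 3 and 3 × 1.5 = 4.5 days (hazard ratio 1.5 if times are exponential), one-sided 5%, 70% power. Follow-up is 14 days (Primary Outcome).

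- Schoenfeld events: 4 × (1.645 + 0.524)² / (ln 1.5)² = 4 × 4.70 / 0.1644, or 115 after rounding up.
- Probability of an event by day 14: 1 − 0.5^(14/3) = 0.961 (TCM); 1 − 0.5^(14/4.5) = 0.884 (control); mean 0.922.
- Per arm: (115 / 2) / 0.922 = 62.3. Freedman's formula gives 118 events, which is 59 per arm without censoring.
- Power at 61 per arm: 122 × 0.922 = 112.5 events; √112.5 / 2 × 0.4055 − 1.645 = 0.506, which gives 69.4%.

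The stated 61 is therefore reproduced, and it belongs to the unadjusted one-sided log-rank test.

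**2. Assumption needed.** The documents do not give the prognostic strength of baseline temperature. It is modelled as a standardised normal covariate with log hazard ratio g per SD. For exponential times its correlation with log time is g / √(g² + π²/6). So g = 0.403 gives 0.403 / √(0.162 + 1.645) = 0.30, and g = 0.740 gives 0.740 / √(0.548 + 1.645) = 0.50.

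**3. Simulated power.** 61 per arm, exponential times, control median 4.5 days, censoring at day 14, one-sided 5%, treatment hazard ratio held at 1.5 at a given temperature.

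| Assumed strength | Log-rank | Cox with baseline temperature |
|---|---|---|
| none | about 70% | about 70% |
| g = 0.2 (weak) | 68% | 69% |
| correlation 0.3 | about 60% | 66–69% |
| correlation 0.5 | about 48% | about 66% |

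The 66–69% is the spread between separate simulation runs. Under no treatment effect, rejection rates were 4.5% to 6.5% across settings for the two tests (2,000 runs each), so about the nominal 5%.

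**4. Sensitivity to the effect assumption.** If the treatment effect is instead raised so that the log-rank test stays near 70%, the log hazard ratio at a given temperature has to be 0.445 (ratio 1.56) at correlation 0.3 and 0.548 (ratio 1.73) at 0.5. Power is then 67% against 74%, and 70% against 88%.

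**5. Sensitivity to the visit schedule.** The Abstract gathers all data at baseline and days 3, 7, 10 and 14. With events recorded only at those four visits (1,500 runs, Efron ties, hazard ratio 1.5), power is 59% against 62% at correlation 0.3 and 46% against 58% at 0.5. With no prognostic effect it is 67% against 65%, where each figure has a simulation standard error of √(0.67 × 0.33 / 1,500), about 1.2 points.

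**The case against.** The strongest reply is that nothing in the primary test is wrong. An unadjusted log-rank test is valid in a randomised trial, it matches the test used for the sample size, and chance imbalance in temperature is already covered by the type I error rate. That stands: this is not bias.

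A second reply is that the plan already allows a Cox model, and that covariate lists often sit in an analysis plan that is not shown. This stands only in part. The protocol does not leave the primary test open. It fixes the unadjusted one and adds a discretionary alternative tied to confounding rather than to prognosis. That wording does not put baseline temperature to planned use.

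A reader might infer that adjustment would lift the trial well above its target, to 74% or 88%. The documents do not support this. Those figures require hazard ratios at a given temperature of about 1.56 and 1.73, and the plan states only a 1.5-fold difference in medians. With 1.5 held at a given temperature, adjustment roughly recovers the planned 70% and does not exceed it. A reader might also infer that the plan rules adjustment out; the Cox clause shows that it does not.

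Finally, the primary outcome is itself unsettled. The Abstract and Sample size describe improvement in any of four symptoms, while Primary Outcome uses fever alone. Under the any-symptom version temperature is not the baseline value of the outcome. That contradiction should be resolved first, and it decides which baseline variable is the right one.

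**Conclusion.** The point holds as one about efficiency and prespecification. By plan, the collected baseline value of the fever outcome is unused in the primary test, and the only route to using it is open to choice after the data are seen.

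The direction is sound and the size is assumed. There is no meaningful difference if temperature is not prognostic and 1 to 2 points if it is weakly so. At correlations of 0.3 and 0.5, with the hazard ratio held at 1.5, the difference is roughly 6 to 9 points and 18 points. It falls to about 3 and 12 points if events are seen only at D3, D7, D10 and D14. These figures rest on exponential times, proportional hazards, a normally distributed covariate and every patient being at risk at D0. The last does not follow from the entry criteria, since patients can enter without fever.

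**What to change.** In Statistical Analysis, replace the optional Cox clause with a prespecified primary analysis: a Cox model with treatment, D0 temperature as a continuous covariate, and pneumonia severity (the minimization factor). State how ties are handled, and say that the model is fitted whatever imbalance is observed. Keep the unadjusted log-rank test and Kaplan-Meier curves as supportive.

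A linear temperature term does not deal with patients who already satisfy the event definition at entry. State either that the fever endpoint is analysed in patients at 37℃ or above at D0, or how the others are counted.

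If the primary outcome is reconciled to the any-symptom version in the Abstract and Sample size, use the baseline score of the four main symptom items in place of temperature.

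The cost is a few sentences and no new data. The small downside is that the hazard ratio becomes conditional on the covariates and relies on proportional hazards, which is why the unadjusted result should be shown beside it.

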**Abstract**

**Introduction:** The outbreak of a novel coronavirus (SARS-CoV-2) and associated COVID-19 disease in late December 2019 has led to a global pandemic. It directly leads to high morbidity and mortality, but also results in a devastating effect on the global economy. Nowadays many trials are underway on this disease to evaluate the efficacy of various therapeutic remedies. This study aims at investigating the effect of Traditional Chinese Medicine, maxingshigan-weijing for treating patients with COVID-19.

**Methods and analysis:** This is an open-label, multicenter randomized controlled clinical trial. One hundred and forty patients infected by SARS-CoV-2 will be randomly assigned to the control group or the experimental group ( Traditional Chinese Medicine, TCM group ) in an equal ratio. The patients in control group will receive routine supportive clinically care including the therapies of anti-viral, anti-bacterial and ameliorating the related symptoms, while patients in TCM group will be asked to take traditional Chinese medicine, maxingshigan-weijing for consecutive 14 days in addition to supportive care. All data will be gathered at baseline and on days 3, 7, 10 and 14. The primary outcome measure will be the number of days till at least one of the clinical symptoms (fever, cough, malaise, shortness of breath) improves in the first 14 days of treatment. Secondary outcome measures will include TCM Syndrome Scoring System and the time of negative of SARS-CoV-2 nucleic acid. A laboratory test will be taken before and after treatment to assess the safety of TCM.

**Discussion:** The study may help to identify the the efficacy and safety of Traditional Chinese Medicine, Maxingshigan-weijing in treating COVID-2019.

**Trial registration:** Chinese Clinical Trial Registry, ChiCTR2000030759. Registered on March 13th 2020, <http://www.chictr.org.cn/.>

**Keywords:** SARS-CoV-2, COVID-2019, Traditional Chinese Medicine ( TCM ), Maxingshigan-weijing decoction, Randomized controlled trial, Protocol

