***Secondary outcomes***

**TCM Syndrome Scoring System**

### TCM Syndrome Scoring System will be used at the baseline and day 3, day 7, day 10 and day 14 of the drug intervention. It is a checklist covering 4 main, 7 secondary and 13 accompanying items. These items are the symptoms and signs summarized by experts according to the clinical manifestations of COVID-2019[24]. The main items consisting of fever, coughing, fatigue and short breath use a four-point scale (0, 2, 4 and 6) depending on the severity; the 7 secondary items including dysphoria, diarrhea, pharyngalgia, expectoration, muscular soreness, nasal obstruction and rhinorrhoea use 0-3-point scale; the 13 accompanying items contain chest pain, headache, aversion to cold, dizziness, nausea and vomiting, anorexia, abdominal distension, dry mouth, anxiety, spontaneous sweating, insomnia, wheezing and blood tinged sputum, and each item is rated on 0-1 scale ( 0 stands for asymptomatic, 1 stands for symptomatic ). The total scores sum up to a range from 0 to 58, with higher scores indicating more severe levels of disease.

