traditional Chinese and western medicine in the treatment of SARS.

Journal of practical internal medicine of traditional Chinese

medicine,2005.19(6):529.

1. Qing Miao, Xiaodong Cong, Bing Wang et. al. Recognition and

reflection of TCM on pneumonia caused by novel

coronavirus.2020,61(2):1-4.

2. JSM P, D P, Yuen KY ea. The Severe Acute Respiratory Syndrome. New Engl J 71. Med.. 2003; 249: 2431-41.

[figure not shown]

|  | **Pre** | **Research Phase** | | | | | | | | | | | | | | **Follow-up** | |
| --- | --- | --- | --- | --- | --- | --- | --- | --- | --- | --- | --- | --- | --- | --- | --- | --- | --- |
| **Time point** | **D0** | **D1** | **D2** | **D3** | **D4** | **D5** | **D6** | **D7** | **D8** | **D9** | **D10** | **D11** | **D12** | **D13** | **D14** | **D7** | **D14** |
| **Research activities** |  |  |  |  |  |  |  |  |  |  |  |  |  |  |  |  |  |
| Enrollment | × |  |  |  |  |  |  |  |  |  |  |  |  |  |  |  |  |
| Eligibility screen | × |  |  |  |  |  |  |  |  |  |  |  |  |  |  |  |  |
| Informed consent | × |  |  |  |  |  |  |  |  |  |  |  |  |  |  |  |  |
| Randomization | × |  |  |  |  |  |  |  |  |  |  |  |  |  |  |  |  |
| **Intervention activities** |  |  |  |  |  |  |  |  |  |  |  |  |  |  |  |  |  |
| TCM + Supportive care |  | × | × | × | × | × | × | × | × | × | × | × | × | × | × |  |  |
| Supportive care |  | × | × | × | × | × | × | × | × | × | × | × | × | × | × |  |  |
| **Baseline assessments** |  |  |  |  |  |  |  |  |  |  |  |  |  |  |  |  |  |
| Socio-demographics | × |  |  |  |  |  |  |  |  |  |  |  |  |  |  |  |  |
| Medical history | × |  |  |  |  |  |  |  |  |  |  |  |  |  |  |  |  |
| Differentiation | × |  |  |  |  |  |  |  |  |  |  |  |  |  |  |  |  |
| Routine inspection | × |  |  |  |  |  |  |  |  |  |  |  |  |  |  |  |  |
| Concomitant medication | × | × | × | × | × | × | × | × | × | × | × | × | × | × | × | × | × |
| **Outcome assessments** |  |  |  |  |  |  |  |  |  |  |  |  |  |  |  |  |  |
| Syndromes Relief | × |  |  | × |  |  |  | × |  |  | × |  |  |  | × |  |  |
| Coronavirus nucleic acid test | × |  |  | × |  |  |  | × |  |  | × |  |  |  | × |  |  |
| TCM Syndrome Scoring System | × |  |  | × |  |  |  | × |  |  | × |  |  |  | × | × | × |

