| **Safety outcomes** |  |  |  |  |  |  |  |  |  |  |  |  |  |  |  |  |  |
| Routine inspection | × |  |  | × |  |  |  | × |  |  | × |  |  |  | × | × | × |
| Urine routine test | × |  |  | × |  |  |  | × |  |  | × |  |  |  | × | × | × |
| Blood rne test | × |  |  | × |  |  |  | × |  |  | × |  |  |  | × | × | × |
| Biochemical test | × |  |  | × |  |  |  | × |  |  | × |  |  |  | × | × | × |
| Electrocardiogram | × |  |  | × |  |  |  | × |  |  | × |  |  |  | × | × | × |
| Adverse events |  | × | × | × | × | × | × | × | × | × | × | × | × | × | × | × | × |

**Fig.2** SPIRIT schedule for enrollment,treatment and assessments.

D day,TCM Traditional Chinese Medicine

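### The protocol fixes plain two-group tests for a symptom score and safety values that also have a baseline measurement: precision is lost, and a t-test does not fit categorical urine and ECG results

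*Protocol*

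**What the plan says.** The STATISTICAL ANALYSIS section of the protocol gives one rule per class of outcome.

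- Secondary outcomes, among them the 0 to 58 TCM symptom score: "For all secondary outcomes, Wilcoxon rank sum test will be used".
- Safety: "two-sided t-test will be applied to each safety measurement after data normalization".
- The only adjusted model is optional and belongs to the primary outcome: "if the influence of confounding factors needs to be considered, Cox proportional hazard model can be used".

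The safety list in the Safety outcomes section contains vital signs and weight, followed by "routine urine test, routine blood test, liver, kidney function tests, and an electrocardiogram".

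The visit lists differ between places:

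- For the score, the text under Secondary outcomes gives baseline and four later visits: "TCM Syndrome Scoring System will be used at the baseline and day 3, day 7, day 10 and day 14 of the drug intervention". The row "TCM Syndrome Scoring System" in Fig. 2 has two follow-up visits as well, so six later visits.
- The laboratory, urine and ECG rows of Fig. 2, such as "Biochemical test", are marked at baseline and the same six later visits. The Abstract describes something narrower: "A laboratory test will be taken before and after treatment to assess the safety of TCM".

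The Randomization section uses minimization on pneumonia severity. That factor does not appear in the analysis of the score or the safety values.

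**The concern.** Two separate weaknesses sit in the same two sentences.

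The first is efficiency. Each of these outcomes has a baseline value and several later ones. A plain two-group test at one later time leaves the variation explained by baseline in the error term. In a trial of 140 patients that variation can be removed at no cost, and doing so also deals with chance imbalance at entry.

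The second is fit. Applied to each safety measurement, the t-test would also cover urine tests and the ECG. These commonly yield graded or normal/abnormal findings, for which a difference in means has no clear meaning and which normalization does not repair. For liver and kidney values the difficulty is different. The Exclusion criteria remove patients with abnormal liver or kidney function, so the useful question is who becomes abnormal. A shift in the mean can stay small while a few of 70 participants per arm have a marked change.

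At stake are the power of the secondary symptom comparison and the ability of the safety analysis to show individual toxicity.

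**Working it through.** **The plan's own figure.** The protocol gives no sample size or power for the secondary or safety comparisons. Its only figure is 61 per arm for the primary log-rank test. With a median ratio of 1.5, one-sided 5% and 70% power, Schoenfeld's formula gives 4 × (1.645 + 0.524)² / (ln 1.5)² ≈ 115 events. Under exponential times with medians 3 and 4.5 days, the event probabilities by day 14 are 0.961 and 0.884, mean 0.922. Then 115 / 0.922 / 2 = 62.3 per arm, close to 61. The primary calculation is reproduced and is not touched by this point. I use 61 per arm below.

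**Precision.** The documents give no correlation ρ between baseline and follow-up, so 0.3 to 0.7 is an assumption. Relative to an unadjusted follow-up comparison (variance 1), baseline adjustment (ANCOVA) leaves 1 − ρ². The equivalent gain in patients is 1/(1 − ρ²) − 1. A test on change from baseline has variance 2(1 − ρ).

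| ρ | Variance left, 1 − ρ² | Cut | Equivalent extra patients | 61 per arm acts like | Change-score variance |
|---|---|---|---|---|---|
| 0.3 | 0.91 | 9% | 10% | 67 | 1.4 |
| 0.5 | 0.75 | 25% | 33% | 81 | 1.0 |
| 0.7 | 0.51 | 49% | 96% | 120 | 0.6 |

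At ρ = 0.7, 0.51 is the share of variance that remains, so the saving is 1 − 0.51 = 0.49 and the gain is 1/0.51 − 1 = 0.96.

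For a 0.5 SD difference at two-sided 5%, power rises from 79% to 83%, 89% and 97%. The difference detectable with 80% power falls from 0.51 SD to 0.48, 0.44 and 0.36 SD. These formulas compare means, so for a rank-based comparison of the score they are approximate.

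**Number of safety tests.** The protocol states no alpha for safety; I assume two-sided 5%. The Safety outcomes section lists 10 headings: 5 vital signs or weight, 4 laboratory panels and the ECG. The analytes within the panels are not listed, so 20 and 30 measurements are assumptions. With no true difference, k tests give 0.05 × k expected signals. The chance of at least one is 1 − 0.95^k if the tests are independent.

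| Measurements | One test each: expected (chance of any) | Six visits each: expected (chance of any) |
|---|---|---|
| 10 | 0.5 (40%) | 60 tests: 3 (95%) |
| 20 | 1.0 (64%) | 120 tests: 6 (99.8%) |
| 30 | 1.5 (79%) | 180 tests: 9 (over 99.9%) |

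Correlation between visits leaves the expected counts unchanged. For 20 measurements at six visits, simulation with a between-visit correlation of 0.5 to 0.7 puts the chance of any signal at 97% to 99%.

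Baseline adjustment does not enter 0.05 × k. Only fewer tests, or estimates with intervals in place of tests, lower the count.

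**The case against.** The best defence has four parts.

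- **The tests are valid.** In a randomised trial an unadjusted two-sample comparison keeps its 5% level, and choosing a more efficient model for a secondary score is partly preference. This stands, so the point on the score is about precision only.
- **The rest may be in the SAP.** The visit, the covariates and the transformation are commonly specified there, and it is not at hand. This stands for the unnamed visit taken alone. It does not answer the tests themselves, because the protocol fixes them for all secondary outcomes and for each safety measurement.
- **Individual toxicity is caught elsewhere.** Adverse events are recorded daily during treatment and at both follow-up visits. This helps only in part: the section on adverse event reporting limits them to events related to the decoction, so they give no fair comparison with control. The scheduled tests carry most of the like-for-like safety evidence.
- **Normalization may mean a transformation towards normality.** That is possible and harmless for skewed continuous values, but it does not make a t-test suitable for categorical findings.

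Two stronger readings are tempting, and the documents support neither. A reader might infer that the unadjusted tests will produce many false safety signals. The protocol calls for a test of each measurement and does not say at each visit; the Abstract even suggests one comparison after treatment. The count also follows from the number of tests, not from the missing adjustment. A reader might also infer that baseline is certainly ignored. The protocol does not say whether raw values or changes are tested, so a test on change is not excluded. Such a test would still be less precise than ANCOVA, as the first table shows.

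**Conclusion.** The point holds in limited form, as an improvement that should be made. The protocol fixes tests with no stated use of baseline or severity for outcomes measured at baseline and up to six later times. The cost in precision is a variance that could be about 9% to 49% lower, equal to 10% to 96% more patients, if the baseline/follow-up correlation is 0.3 to 0.7. That range is assumed and is only approximate for the rank-based score.

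The t-test is wrong as written for urine and ECG results recorded as categories, and a comparison of means is a weak tool for finding a few marked abnormalities. This part rests on the usual form of such results, because the protocol does not list the individual readouts.

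Multiplicity in safety is modest, about 0.5 to 1.5 chance signals, if each of 10 to 30 measurements is tested once. It reaches 3 to 9 only if every visit is tested. The primary comparison and its sample size are not affected.

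**What to change.** Replace the two sentences in STATISTICAL ANALYSIS along these lines.

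- **TCM score:** a repeated-measures model with baseline score, pneumonia severity, arm, visit and arm-by-visit, with the day-14 difference between arms as the single estimate. Use rank ANCOVA with the same two covariates if the score is clearly skewed. Day 14 is in both the text list and Fig. 2.
- **Continuous safety values:** one baseline-adjusted mean difference with confidence interval per measurement, on the clinical scale, in place of a test on normalized data.
- **Urine, ECG and liver/kidney tests:** shift tables, with the number of participants in each arm moving from normal to abnormal, in place of the t-test.
- **Visit lists:** reconcile the Abstract, the text on the TCM score and Fig. 2, so that the same visits are named in each.

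The cost is a change of wording and slightly more analysis work. The scheduled measurements are enough, so no new data are needed.
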